### Intervention: online interpersonal psychotherapy and telephone coach

Participants in the intervention group will be asked to complete six, 30-min online interactive IPT modules over a 6-week period. Modules will be embedded in an online app that participants access with a personalized login username and password. The topics covered in the modules are: 1) identifying the important relationships in their life; 2) understanding and improving communication patterns; 3) navigating interpersonal disputes; 4) adapting to role transitions; 5) working through grief and loss; and 6) maintaining IPT strategies following study completion. These topics were designed based on the work of Stuart and Robertson and tailored to pregnancy [23]. Participants are asked to complete specific assignments online for each module such as self-awareness homework, exploring relationships with those closest to you. Goals of the intervention include symptom relief [54], improving interpersonal functioning and relationships [22, 23], changing expectations about interpersonal relationships [49], and improving participant social support networks [23]. Participants are guided to recognize and disengage from unhelpful communication patterns and develop strategies for engaging social supports in navigating challenging times such as grief and loss, role transitions, and conflict with their partner or extended family members [55].

Participants in the intervention group will receive psychosocial assessments using the questionnaires outlined in Fig. 1. These questionnaires will be administered at 3 months postrandomization and again at 3 and 6 months postpartum.

Telephone coaches will be available to the intervention group at any time; however, the coaches also contact women under specific conditions, including having very high symptoms of depression, anxiety or stress, experiencing a pregnancy loss during their study participation, or having complex needs (e.g., high psychological and social needs). Telephone coaches consist of a social worker and a nurse who have identical formal IPT, suicide assessment and prevention, interviewing, and counseling training. Coaches are supervised weekly to address and maintain fidelity in the study protocol.

### Control condition: routine prenatal care

Participants in the control group will receive routine prenatal care which usually does not include standardized psychosocial assessment and, in most cases, treatment. Women in the control group of this study will receive psychosocial assessments using the same questionnaires at the same time points as those administered to the intervention group.

### Both groups

All applicants will complete the Depression, Anxiety, and Stress Scale-21 (DASS21) and the Edinburgh Postnatal Depression Scale (EPDS) on recruitment (prerandomization) to provide baseline data on their mental health status. All participants (control and intervention groups) assessed as having thoughts of self-harm will receive a computerized message offering then crisis line/emergency room contact information and informing them that they will be contacted by the study nurse. Following randomization, participants will complete the baseline series of questionnaires which comprehensively assess a variety of demographics and psychosocial constructs (T_1_) (Fig. 1). These questionnaires will be completed again at 3 months postrandomization (T_2_), after 8 months of pregnancy (T_3_), and 3 months postpartum (T_4_).

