### Methods to protect against bias: randomization and blinding

Eligible women will complete the consent to participate in the online app and will then be automatically randomized within the app at a 1:1 control to treatment ratio. Immediately following randomization women will be notified of their group assignment through the app. Participants are not blind to their group allocation, nor are their health-care providers who are informed of the screening results of their patients (if the participant consents to fax a report to her health-care provider) and recommendation for e-IPT.

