##### Variables

Variables that are associated with (and may mediate) the effectiveness of the e-IPT will be explored through an examination of variables that may be influential in the perinatal mental health theories and literature. The factors to be included were selected based on their association with perinatal depression, anxiety and stress. As a result, the influence of self-efficacy, social support, sense of mastery, self-esteem, sleep, coping, and resilience will be explored. Additionally, the association of preconception of mental health problems such as borderline personality disorder, perfectionism, and attention deficit/hyperactivity disorder will be investigated. These variables will be included as covariates in the data analysis models.

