### Data collection

There are three data collection points for both intervention and control groups: recruitment (T_1_), 3 months postrandomization (T_2_), after 8 months of pregnancy (T_3_), and 3 months postpartum (T_4_)_._ (Fig. 1). All questionnaires will be completed online though a web application. Participants will receive computer-generated emails or smartphone reminders to complete questionnaires. These reminders will occur at 1, 3, and 7 weeks.

In addition to the online questionnaires and online modules, participants in the intervention group will be asked to participate in interviews regarding the feasibility and acceptability of the intervention. Additionally, women will be asked about suggestions for improving the e-IPT. Thirty women in the intervention group will complete the interviews. Using a semistructured interview schedule, these women will be asked about their experiences with the online intervention. These interviews will be transcribed verbatim and then coded and analyzed using an inductive thematic analysis approach [76].

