#### Quantitative analysis

The quantitative dataset will be analyzed using IBM SPSS Statistics software. Missing values will be managed by using multiple imputation [78]. Assessment of the presence of any outliers will be made, and it will be determined if they are true values or data entry errors [78]. If not determined as an entry error, the analysis will be run with the outliers included and then run without the outliers included. Results will be compared and whether the outliers skew the results and what it means on a clinical level will be reported. If the results do not differ, then the analysis with the outliers included will be used. Outcomes will be assessed based on the number of modules completed. Additionally, a sensitivity analysis will be completed by running a negative binomial regression model which accounts for variance in the data. Descriptive statistics (mean/standard deviation or frequency/proportions) will serve to describe the characteristics of participants and assess group equivalence at baseline. Repeated measures analysis of variance will be used to determine the effectiveness of the intervention. The variables will be included in the analysis as covariates and bivariate analysis will be performed first. Those variables found to be statistically significant at the bivariate level will be included in the multivariate model. Analysis will adhere to the intent-to-treat principle [78].

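### Apart from the DASS21 and EPDS, the T1 baseline questionnaires are completed after each woman knows her arm, so relationship quality and the psychosocial covariates have no described pre-allocation value

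*Protocol article*

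**What the plan says.** The order of events comes from two sections of the protocol article.

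- *Both groups* (after the control condition): the DASS21 and EPDS are completed "on recruitment (prerandomization) to provide baseline data on their mental health status". The next step is stated as "Following randomization, participants will complete the baseline series of questionnaires which comprehensively assess a variety of demographics and psychosocial constructs", and this is labelled T1.
- *Methods to protect against bias: randomization and blinding*: "Immediately following randomization women will be notified of their group assignment through the app", and "Participants are not blind to their group allocation".

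The uses of baseline information are in two other sections.

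- *Variables*: "the influence of self-efficacy, social support, sense of mastery, self-esteem, sleep, coping, and resilience will be explored", and "These variables will be included as covariates in the data analysis models".
- *Quantitative analysis*: descriptive statistics will "describe the characteristics of participants and assess group equivalence at baseline". Effectiveness is judged by repeated measures analysis of variance, with covariates screened in by bivariate significance.

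*Data collection* dates T1 differently: "There are three data collection points for both intervention and control groups: recruitment (T_1". The abstract places T1 at baseline in pregnancy without saying on which side of randomisation it falls. It also implies that depression, anxiety and stress are measured at T1.

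**The concern.** A baseline protects a randomised comparison because allocation cannot have influenced it. Here the T1 scales are self-reports by women who have just learned whether they will receive the programme. A woman told she will get help with her relationships, or that she will not, may answer relationship, coping or self-efficacy items differently on that account. She may also be more or less likely to finish T1 at all.

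Three between-arm uses are exposed if T1 serves as the baseline:

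- a group-by-time contrast starting from T1;
- a model adjusted for T1 values;
- the equivalence check, which could no longer separate chance imbalance from reaction to allocation.

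Multiple imputation of missing T1 answers does not help, because it would impute a post-allocation value.

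The pilot is meant to optimise the processes of the full trial, so an uncorrected order could be carried into a study planned at 816 women.

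**Working it through.** **1. Order of events.** There is no stated figure to reproduce, so the check is one of sequence.

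| Measure | Described pre-randomisation value? | Source |
|---|---|---|
| DASS21, EPDS | Yes | *Both groups* |
| Relationship quality (secondary objective 2) | None described | *Both groups*; Table 2 |
| Self-efficacy, social support, mastery, self-esteem, sleep, coping, resilience | None described | *Both groups*; *Variables* |
| Age, ethnicity, number of children and similar | Collected at T1, but hardly open to reporting bias | *Both groups*; *Demographic assessment* |

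**2. Consistency of the timing.** *Both groups* puts T1 after randomisation, while *Data collection* equates T1 with recruitment. The randomisation section goes from consent directly to randomisation and mentions no questionnaire in between. It is also unclear whether the DASS21 and EPDS are repeated within T1 and, if so, which value counts as baseline.

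**3. Size, as an illustration.** The documents give neither a shift nor a correlation, so both are assumed. Let s be the shift in measured T1 between arms caused by the allocation news (in SD), r the correlation of T1 with follow-up, and the true effect zero. With 80 women per arm:

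- Adjusted for T1: bias = −r × s, standard error = √[(2/80)(1 − r²)].
- Change from T1: bias = −s, standard error = √[(2/80) × 2(1 − r)].

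Worked example, s = 0.2 and r = 0.5:

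- Adjusted: bias = −0.5 × 0.2 = −0.10; standard error = √(0.025 × 0.75) = 0.137.
- Change: bias = −0.20; standard error = √(0.025 × 2 × 0.5) = 0.158.

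The type I error is for a two-sided test at nominal 5%, by normal approximation.

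| s | r | Bias, adjusted | Type I error | Bias, change | Type I error |
|---|---|---|---|---|---|
| 0.1 | 0.3 | −0.03 | 5.5% | −0.1 | 8.3% |
| 0.1 | 0.5 | −0.05 | 6.5% | −0.1 | 9.7% |
| 0.1 | 0.7 | −0.07 | 9.5% | −0.1 | 12.9% |
| 0.2 | 0.3 | −0.06 | 6.8% | −0.2 | 18.8% |
| 0.2 | 0.5 | −0.10 | 11.3% | −0.2 | 24.4% |
| 0.2 | 0.7 | −0.14 | 23.6% | −0.2 | 37.2% |
| 0.3 | 0.3 | −0.09 | 9.2% | −0.3 | 36.1% |
| 0.3 | 0.5 | −0.15 | 19.5% | −0.3 | 47.5% |
| 0.3 | 0.7 | −0.21 | 46.0% | −0.3 | 68.8% |

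A simulation with 400,000 women agreed with the two bias formulas (−0.031 to −0.211 adjusted, −0.094 to −0.304 for change). With s = 0 the bias is zero. The sign depends on which way, and in which arm, the answers move, and the documents do not settle that.

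**The case against.** The strongest reply is that the exposure is narrower than the stated order suggests, and most of that reply stands.

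- The main symptom scales have a pre-randomisation value. A reader might infer that every baseline value is contaminated, but the text on the DASS21 and EPDS contradicts this.
- A reader might infer that the primary outcome is compromised. The feasibility and acceptability percentages are described within the intervention arm and use no between-arm T1 contrast. Secondary objective 3 is also set within that arm, where every woman received the same news, so the between-arm formulas do not apply to it.
- It is tempting to divide the illustrated bias by the planning effect of d = 0.50 and call the result a share of the effect lost. That effect was planned for depression on the DASS21, which has a protected baseline. No effect size is planned for the exposed scales, so the ratio has no basis.
- The protocol does not say which time points enter the repeated measures analysis, or at which time point the covariates are taken. That detail may properly sit in an analysis plan. Treating T1 as the baseline is the natural reading of its label, but it is an inference.

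The reply does not remove the core. For relationship quality and the psychosocial covariates, T1 is the earliest measurement described. An analysis plan could decline to use T1 as a baseline, but it could not supply a pre-allocation value that was never collected.

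**Conclusion.** The point holds in a limited form. As written, T1 other than the pre-randomisation DASS21 and EPDS is collected after disclosure of the arm. Relationship quality and the seven psychosocial covariates therefore lack a described pre-allocation baseline. Any between-arm analysis that starts from T1, adjusts for these scales at T1, or judges equivalence on them is open to bias from reaction to allocation and from differential completion.

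Under the assumed ranges the bias is about 0.03 to 0.21 SD with adjustment and 0.1 to 0.3 SD for change from T1. Those figures show what a modest reaction would do; they are not evidence that one occurs. The pre-randomisation DASS21 and EPDS values, the within-arm primary percentages and follow-up comparisons made without T1 are unaffected. Fixed demographics are little open to reporting bias, though they can still be missing differently by arm.

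**What to change.** 1. Reconcile *Both groups*, the randomisation section, *Data collection* and the abstract (and check the SPIRIT schedule in Fig. 1) so that they give one sequence: consent, the whole T1 battery submitted in the app, randomisation, disclosure of the arm. Apply it to the remaining pilot recruitment and to the full trial. State which DASS21 and EPDS measurement is the baseline.
2. For women randomised under the present order, use the pre-randomisation DASS21 and EPDS and fixed demographics as baseline covariates. Compare the other scales between arms at follow-up, without T1 adjustment and without change from T1.
3. Count the women who stop during T1 and report them, before and after the change.

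The cost is a re-ordering of app screens and a short amendment. Some women will stop before randomisation instead of after it. Recruitment began in March 2019, so the pilot would contain two cohorts with different baseline timing, and the report should say so.

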### Methods to protect against bias: randomization and blinding

Eligible women will complete the consent to participate in the online app and will then be automatically randomized within the app at a 1:1 control to treatment ratio. Immediately following randomization women will be notified of their group assignment through the app. Participants are not blind to their group allocation, nor are their health-care providers who are informed of the screening results of their patients (if the participant consents to fax a report to her health-care provider) and recommendation for e-IPT.

### Definition and measurement of outcomes

#### Primary outcomes

The primary outcome of this pilot study is the feasibility and acceptability of e-IPT for pregnant women. Feasibility of the e-IPT intervention will also include an examination of enrollment and retention of women in the study. Additionally, the assessment of feasibility will assess adherence to the planned methods of data collection and intervention delivery. The feasibility interviews with 30 participants in the intervention group will ask women to comment on how easy it was to access and complete the intervention, as well as how long it took to complete the modules. In this study we also define feasibility as the percentage of women in the intervention group who report that the e-IPT intervention is easily done as a component of care during the perinatal period. Women in the e-IPT intervention group will also answer questions rating their experiences of the intervention. Women in the intervention group will answer questions to assess their views of e-IPT (for example, ‘were you comfortable using e-IPT with an online coach for therapy?’). Women in the intervention group will also be asked about suggestions for improving the e-IPT.

In this study we define acceptability as the percentage of participants in the intervention group who report that e-IPT is acceptable, the percentage of participants reporting that the e-IPT modules were easy to understand and navigate, the percentage of participants who found that the information in the module was effective in achieving intended outcomes, and whether the exercise was clear and easy to understand. Additionally, participants in the intervention group will be asked whether they would recommend the module to a pregnant friend. Women receiving the e-IPT will also be asked several questions to evaluate their user experience with the modules.

#### Strategies for assessing adherence and attrition

To assess adherence, the completion of online questionnaires and the intervention homework will be recorded through a specific application through Google Analytics. This application will include the length of time taken to complete modules and the number of modules completed. To assess attrition, comparisons between the attrition rates of the control and the intervention groups will be performed.

#### Secondary outcomes

##### Psychological outcomes

Secondary outcomes of this pilot study evaluate the effectiveness of e-IPT compared to routine prenatal care with respect to a variety of intraindividual and interpersonal outcomes (Table 2), specifically stress, anxiety, depression, and relationship quality in prenatal women. The DASS21 is a 21-item questionnaire used to examine three self-report subscales including depression, anxiety, and stress over the previous week. Responses are recorded on a Likert-type scale ranging from 0 (not applicable at all) to 3 (applicable very much of the time) [56]. Based on the scores of each domain (raw scores multiplied by 2) the severity is graded into normal, mild, moderate, severe, or extremely severe [56]. The DASS21 is a well-validated (concurrent validity coefficients were 0.87 and 0.84) and reliable (test–retest and split-half reliability coefficient scores of 0.99 and 0.96) questionnaire [57] that has been previously used in perinatal samples [58–61]. The EPDS will be used to assess symptoms of depression experienced during pregnancy and the postpartum period. The EPDS is a well-validated questionnaire that has been previously used in pregnant women [62–65]. The EPDS is a 10-item self-report questionnaire used to assess perinatal depression (eight items) and anxiety (two items) over the previous week [66]. The questions are a Likert scale scored from 0 to 3 (with every changing anchors) with higher scores indicating more depressive symptoms. The EPDS is well validated, with sensitivity and specificity of 86% and 78%, respectively [67]. There is also good reliability for the EPDS, with test–retest reliability of 0.92 [68]. Additional secondary outcomes will be evaluated including relationship quality, resiliency, maternal–infant attachment, infant behavior, and parenting stress/competence.

##### Variables

Variables that are associated with (and may mediate) the effectiveness of the e-IPT will be explored through an examination of variables that may be influential in the perinatal mental health theories and literature. The factors to be included were selected based on their association with perinatal depression, anxiety and stress. As a result, the influence of self-efficacy, social support, sense of mastery, self-esteem, sleep, coping, and resilience will be explored. Additionally, the association of preconception of mental health problems such as borderline personality disorder, perfectionism, and attention deficit/hyperactivity disorder will be investigated. These variables will be included as covariates in the data analysis models.

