**Methods:**

A pilot randomized controlled trial design with repeated measures will evaluate the feasibility and acceptability of e-IPT for pregnant women compared to routine prenatal care. Qualitative interviews with 15–30 individuals in the intervention group will provide further data on the feasibility and acceptability of the intervention. Assessment of feasibility will include the ease of accessing and completing the intervention. Women will also be asked about what barriers there were to starting and completing the e-IPT. Assessment of acceptability will inquire about the perception of women regarding the intervention and its various features. A sample size of 160 consenting pregnant women aged 18 years and older will be enrolled and randomized into the experimental (e-IPT) or control (routine care) condition. The secondary outcome measures include: depression, anxiety and stress symptoms; self-efficacy; self-mastery; self-esteem; relationship quality (spouse, immediate family members); coping; and resilience. All participants will complete the aforementioned measures at baseline during pregnancy (T_1_), 3 months postrandomization (T_2_), at 8 months of pregnancy (T_3_), and 3 months postpartum (T_4_).

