### Interpersonal psychotherapy: aim and effectiveness

The aim of IPT is to improve social support networks since enhanced social support predicts greater psychological adjustment to stressors; IPT is therefore a promising intervention for prenatal women [18–21]. IPT is a short-term dynamic attachment-based psychotherapy [22, 23] aimed at symptom reduction and improved interpersonal relationships through enhanced social support [23]. The primary foci of treatment with IPT are the interpersonal issues of grief and loss, interpersonal disputes, and role transitions (Stuart, 2012). IPT attempts to provide clarification of individuals’ feelings, expectations, interactions, social roles, education, and social competence [24]. Additionally, IPT practitioners endeavor to assist individuals in establishing or better mobilizing support networks [23]. Individual functioning is believed to be based on a combination of intrapersonal factors (temperament, personality and attachment style) in relation to interpersonal factors (social support and quality of relationships) [23].

IPT is a highly effective treatment for depression and anxiety [25–30]. Randomized controlled trials of IPT in perinatal women found that IPT improved symptoms of depression and anxiety [20, 31–35] and functioning [9, 36]. The US Preventive Services Task Force showed convincing evidence that IPT is effective in preventing perinatal depression [13]. A 2011 meta-analysis found that IPT was more effective than CBT for treating perinatal depression [36]. A 2011 meta-analysis also found that IPT was more effective than couples therapy in the treatment of depressive symptoms during the perinatal period [37].

Automatic internet-based therapy interventions offer access to psychological resources at reduced costs, can be accessed from across the world, and can be accessed at any time. Research supporting the use of internet interventions for the prevention and treatment of perinatal mental health concerns is limited but several trials have demonstrated preliminary effectiveness in the prevention [38–40] and treatment of postpartum depression [41–43]. The recommendations from the gaps in the literature leads towards a trial of online IPT (e-IPT). To date, no trials have focused on improving psychological distress in prenatal women as a result of receiving e-IPT.

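### Social support, the stated aim of IPT and a goal of e-IPT, is in none of the secondary outcome lists and has only a covariate role, not limited to baseline values; the outcome lists also disagree

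*Protocol article*

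**What the plan says.** In the Protocol article, the Background section on the aim and effectiveness of IPT states: "The aim of IPT is to improve social support networks since enhanced social support predicts greater psychological adjustment to stressors". The Intervention section lists four goals for e-IPT: symptom relief, better interpersonal functioning and relationships, changed expectations of relationships, and "improving participant social support networks".

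The Variables section opens with "Variables that are associated with (and may mediate) the effectiveness of the e-IPT will be explored" and then says that "the influence of self-efficacy, social support, sense of mastery, self-esteem, sleep, coping, and resilience will be explored". It closes by assigning these variables to the models as covariates. The Quantitative analysis section repeats the covariate role and adds a screening step: variables significant in bivariate analysis go into the multivariate model.

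Secondary outcomes are listed in four places:
- Abstract, Methods: "The secondary outcome measures include: depression, anxiety and stress symptoms; self-efficacy; self-mastery; self-esteem; relationship quality (spouse, immediate family members); coping; and resilience".
- Research objectives text: anxiety, depression, overall distress, relationship quality and maternal resilience.
- Table 2, objectives 1 and 2: stress, anxiety, depression and relationship distress.
- Psychological outcomes: stress, anxiety, depression and relationship quality, followed by "Additional secondary outcomes will be evaluated including relationship quality, resiliency, maternal–infant attachment, infant behavior, and parenting stress/competence".

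Table 2, objective 3, covers factors, mediators and moderators, and confines the question to the intervention group.

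**The concern.** A variable that the treatment is designed to change is normally compared between arms. Here it is named as a target, then handled as something to adjust for. Two consequences follow.

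First, if the covariate is a follow-up value, the adjusted treatment effect on symptoms no longer includes the part that works through social support. The pilot is meant to inform the full trial, and an estimate reduced in this way would misinform it.

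Second, the route by which the protocol hopes to learn about mechanism, the mediator objective, cannot deliver it from one arm.

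Separately, because the outcome lists differ, a reader of the results could not tell which between-arm comparisons were prespecified as secondary and which were exploratory.

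**Working it through.** No figure in the plan bears on this point, so there is nothing to reproduce. The check sets the sections side by side.

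**Step 1: constructs by section.**

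| Construct | Abstract | Objectives text | Table 2, obj. 1–2 | Psychological outcomes | Variables (covariate) |
|---|---|---|---|---|---|
| Depression | yes | yes | yes | yes | – |
| Anxiety | yes | yes | yes | yes | – |
| Stress | yes | as overall distress | yes | yes | – |
| Relationship quality or distress | yes | yes | yes | yes | – |
| Resilience | yes | yes | – | yes | yes |
| Self-efficacy | yes | – | – | – | yes |
| Mastery | yes | – | – | – | yes |
| Self-esteem | yes | – | – | – | yes |
| Coping | yes | – | – | – | yes |
| Mother–infant attachment | – | – | – | yes | – |
| Infant behaviour | – | – | – | yes | – |
| Parenting stress/competence | – | – | – | yes | – |
| Social support | – | – | – | – | yes |
| Sleep | – | – | – | – | yes |

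**Step 2: counts.**
- Social support is in 0 of 4 places, or 0 of 5 lists if the main and additional lists under Psychological outcomes are counted separately.
- The Abstract has 9 constructs. Psychological outcomes has 8, or 9 if parenting stress and parenting competence are split. Shared: depression, anxiety, stress, relationship quality and resilience, so 5.
- Only in the Abstract list: 9 − 5 = 4. Only in the Psychological outcomes list: 8 − 5 = 3, or 9 − 5 = 4.
- The Variables section names 7 influencing variables. Five (self-efficacy, mastery, self-esteem, coping, resilience) are also outcomes in the Abstract, which leaves 7 − 5 = 2: social support and sleep.

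**Step 3: what the covariate role does.** Let allocation be A, follow-up social support M and a symptom score Y. In linear models without interaction,

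M = i₁ + a·A + e₁ and Y = i₂ + c′·A + b·M + e₂.

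Substituting the first into the second gives the total effect of allocation, c = c′ + a·b. A model that adjusts for M estimates c′ and drops a·b, the part that the Background says IPT works through. The bivariate screen does not protect against this: a variable strongly related to Y is the kind that passes it. If M is a value unaffected by allocation, then a = 0 for that value and the adjustment removes nothing.

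**Step 4: what the mediator objective can show.** Mediation needs a, the effect of A on M. Within the intervention group A is constant, so a cannot be estimated. Objective 3 can describe how M and Y move together in treated women, but not whether e-IPT changed M.

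**Step 5: is M available at follow-up?** The section headed Both groups says that the baseline series is repeated at T2, T3 and T4. No social support instrument is named, and Fig. 1, the assessment schedule, is not in the text at hand. Repeated measurement is therefore an inference.

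**The case against.** Several arguments on the other side carry weight.

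- A reader might infer that the trial never tests what e-IPT is meant to change. The text does not support that. The Background also describes IPT as directed at symptoms and relationships, and of the four goals, symptom relief and relationships are compared between arms; relationship distress has its own objective and hypothesis. What lacks a comparison is social support itself, which the Intervention section lists as a goal separate from relationships.
- A reader might infer that the plan does adjust for follow-up social support. It does not say so. Neither section states which values are used, and an analysis plan may settle it. What stands is that the wording permits follow-up values for variables that the same section calls possible mediators.
- A reader might take it that all 160 women could be compared at three follow-ups at no extra burden. That rests on the unseen schedule and ignores dropout. If the full-trial rates under Sample size estimation (25% attrition, 5% loss to follow-up) applied to the pilot, about 160 × (1 − 0.25 − 0.05) = 112 would remain, or 160 × 0.75 × 0.95 = 114 if the losses compound. The article also gives a second schedule, with 3 and 6 months postpartum, in Study design and Intervention.
- Exploratory mediation is a legitimate role for a mechanism variable. That stands in principle, but not for an analysis confined to one arm.
- The lists use open wording, and one is in an abstract. This softens the disagreement but does not remove it: four constructs are outcomes in the Abstract and, in the body, appear only as covariates.
- To call a change in social support the best evidence that the online format works would be opinion. The primary outcome is feasibility and acceptability, assessed by retention, module completion and women's reports.

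**Conclusion.** The point holds in limited form. Social support is the stated aim of IPT and one of four goals of e-IPT, yet it is in no secondary outcome list. Its only modelling role is as a covariate with no restriction to baseline, and the mediator objective is confined to one arm. The outcome lists share 5 constructs out of 9 in the Abstract and 8 or 9 under Psychological outcomes, and five constructs are both outcomes and covariates.

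The size of any bias cannot be computed, because the documents give neither a nor b. It is zero if only values unaffected by allocation are used, and a·b if follow-up values are used. That social support is collected at follow-up is an assumption from the Both groups and Variables sections. The matter concerns secondary analyses and what is carried into the full trial; the primary feasibility and acceptability conclusion is not affected.

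**What to change.** 1. In Variables and Quantitative analysis, state that social support and the other possible mediators enter effect models at baseline values only. Both groups places the T1 series after randomization, and women are told their allocation at once, so also state that these values are collected before allocation is known or, failing that, before the first module.
2. Where social support is collected at follow-up, compare it between arms as a secondary or exploratory outcome, labelled as such, at the follow-up visits of whichever schedule the article settles on.
3. Reword Table 2, objective 3, so that any mediator analysis uses both arms, or describe it as association within the intervention group.
4. Use one secondary outcome list in the Abstract, the objectives text, Table 2 and Psychological outcomes, and label everything else exploratory.

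The cost is wording plus one added comparison in a pilot. If Fig. 1 shows that social support is not measured after baseline, item 2 would need an added questionnaire or should be dropped; the other items still apply.
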